### Sample size and recruitment

2.32

At least 52 children and adolescents of both sexes, aged between 8 and 18 years old, will be recruited from the Pediatric Endocrinology Unit at University Hospital of Navarra (Pamplona, Spain). This sample size was determined based on the results of a previous meta-analysis (12), which suggested an expected effect size on daily insulin dose requirements of 0.81. Using the G*Power software (58) and considering a power of 0.80, a significance level of 0.05 and accounting for a dropout of 15% (59, 60), a minimum of 26 children and adolescents per group is required.

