**Methods and analysis:**

A minimum of 52 children and adolescents aged 8-18 years, who were diagnosed with T1DM at least 6 months ago, will be randomly assigned to either a group engaging in an individualized resistance exercise program at least 3 times per week over a 24-week period or a waiting-list control group. The primary outcome will be the daily insulin dose requirement. The secondary outcomes will include glycemic control, cardiometabolic profile, body composition, vascular function, physical fitness, 24-hour movement behaviors, diet, and psychological parameters. The usability of the app will also be assessed.

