## Introduction

1

Type 1 diabetes mellitus (T1DM) imposes a substantial burden on children and adolescents worldwide. According to estimates from the International Diabetes Federation (IDF), 1.2 million individuals under age 20 have T1DM globally (1). Not maintaining optimal glycemic control is associated with chronic health issues later in life. However, achieving and sustaining appropriate glycemic control poses a significant challenge for young individuals with T1DM, particularly during the transition from childhood to adulthood. Inadequate glycemic control in T1DM patients can lead to long-term complications including cognitive dysfunction (2), cardiovascular disease (3), diabetic neuropathy (4), diabetic retinopathy (5), chronic kidney disease (6), diabetic foot ulcers (7), and dry skin (8). While technology has enhanced self-management capacity (9), novel strategies that are accessible and cost-effective are urgently needed to improve glycemic control in young T1DM patients.

The American Diabetes Association (ADA) recommends that individuals under 20 years old with diabetes engage in 60 minutes of moderate to vigorous aerobic physical activity daily. This should be paired with vigorous muscle-strengthening and bone-strengthening activities at least three days per week (10). However, children and adolescents with T1DM are less active, more sedentary, and less fit than their healthy counterparts (11). A recent meta-analysis showed that exercise training has a moderate effect on reducing glycated hemoglobin (HbA1c) and insulin dose per day in youths with T1DM (12). Specifically, resistance training seems to be one of the most effective strategies for improving glycemic control among children and adolescents with T1DM (13). In adults, resistance exercise has proven efficacy in minimizing exercise-induced hypoglycemia risk in T1DM (14, 15). However, lack of awareness and fear of hypoglycemia can discourage young people from participating in physical activities, especially resistance exercise (16). This highlights the need for new technologies to support the T1DM population in managing hypoglycemia situations and promoting exercise.

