### Randomization, allocation concealment, and blinding

2.33

Participants meeting eligibility criteria will be randomly assigned to one of two groups in a 1:1 ratio using block randomization with a computer-generated schedule (Research Randomizer V.4). This will ensure equal group sizes. Randomization will continue until a predetermined number of participants are assigned. The allocation code will be kept confidential at Navarrabiomed until final analysis. To ensure blinding, each study group will be assigned an alpha-numeric code. Researchers will receive the code for their assigned group. Data analysts will not have access to the code until completing the coded intervention analysis. Due to the nature of the study, patients in the Diactive-1 App group will not be blinded.

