### Statistical methods

2.36

The quantitative variables will have their mean (M) and standard deviation (SD) provided, whereas the qualitative variables will include frequencies (n) and percentages (%). To assess data normality visual inspection of Q-Q plots and Shapiro-Wilk test will be used. For the homogeneity of variances, Levene’s test will be used. Subsequently, for two-group comparisons, either Student’s t-test or Mann–Whitney U test will be used based on adherence to the normality assumption.

Associations among qualitative variables will be examined using Pearson’s chi-square (χ²) test. For quantitative variables, the association will be tested using Spearman’s rank correlation coefficient (ρ) or Pearson’s correlation coefficient (r), depending on the assumption of normality. Initial analyses will establish frequency, range, variability, and distribution patterns of each variable, guiding the choice of the most appropriate statistical test for comparisons.

Given the experimental design of this RCT involving two data collections—baseline (t0 = 0 weeks) and post-intervention (t1, t2 = 12 and 24 weeks)—in both intervention and control groups, a comparative analysis will be conducted to identify intergroup differences. Multilevel mixed-effects regression models with repeated measures will be used to evaluate the intervention effect for each dependent variable. Multivariate analyses will account for autocorrelation between repeated measures.

For data analysis, both intention-to-treat (ITT) and per-protocol (PP) approaches will be employed. ITT measures the impact of intervention assignment, while PP analysis gauges the effect of intervention receipt. Statistical analyses will be performed using Stata software (version 17.0) (StataCorp, College Station, TX, USA), the statistical software R (Version 4.1.1) (R Core Team, Vienna, Austria), and RStudio (Version 2021.09.2) (Posit, Boston, MA, USA). Statistical significance will be determined by a p-value ≤ 0.05.

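### Section 2.32: 26 per group does not follow from the stated inputs under a conventional two-sided t-test; after 15% dropout the power is about 0.75, not 0.80

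*Protocol article*

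**What the plan says.** Section 2.32 (Sample size and recruitment) takes its effect size from a meta-analysis, "which suggested an expected effect size on daily insulin dose requirements of 0.81". It names G*Power and sets the remaining inputs: "considering a power of 0.80, a significance level of 0.05 and accounting for a dropout of 15" per cent. The result is that "a minimum of 26 children and adolescents per group is required". The abstract repeats the total: "A minimum of 52 children and adolescents aged 8-18 years".

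Section 2.33 fixes the allocation: participants are "randomly assigned to one of two groups in a 1:1 ratio".

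The article states neither the G*Power test family nor whether the test is one-sided or two-sided, and it gives no correlation between repeated measurements. Section 2.36 gives only a threshold: "Statistical significance will be determined by a p-value ≤ 0.05". It names Student's t-test or the Mann–Whitney test for two-group comparisons, and multilevel mixed-effects models with repeated measures for the intervention effect.

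**The concern.** All the usual inputs and the result stand in one short paragraph, so the result can be checked. Under the default reading (two independent means, two-sided 5% level), the number required with no dropout at all is already 25 per group. That leaves room for one extra child per group, where a 15% allowance needs four or five.

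This is the only sample-size justification in the article, and readers will use it to interpret a null result on daily insulin dose. If a trial that enrols exactly the stated minimum and loses the stated 15% has a type II error of about 25% rather than 20%, the published figure gives more assurance than the design provides.

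**Working it through.** **Inputs.** Standardised effect d = 0.81, power 0.80, significance level 0.05, dropout 15% and 26 per group (all section 2.32); 1:1 allocation (section 2.33). Sidedness and test are not stated, so two-sided and a two-sample t-test are assumed first.

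**Formula.** With n evaluable per group, the t statistic has 2n − 2 degrees of freedom and noncentrality d x √(n/2). Power is the probability that it falls beyond the two-sided 5% critical value.

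**Step 1: try to reproduce 26.**

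| Evaluable per group | Two-sided power, d = 0.81 |
|---|---|
| 22 | 0.747 |
| 24 | 0.784 |
| 25 | 0.801 |
| 26 | 0.817 |

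So 25 evaluable per group are needed. Adding dropout:
- 25 / (1 − 0.15) = 29.4, so 30 per group (60 in total).
- The cruder 25 x 1.15 = 28.75, so 29 per group (58 in total).

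The normal approximation needs 24 evaluable, hence 24 / 0.85 = 28.2, so 29, or 24 x 1.15 = 27.6, so 28. None of these gives 26.

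**Step 2: what 26 randomised delivers.** 26 x 0.85 = 22.1, so about 22 evaluable per group. Noncentrality is 0.81 x √11 = 2.69 on 42 degrees of freedom, and power is 0.747. The effect detectable with 0.80 power at 22 per group is 0.865. With no dropout, 26 per group has power 0.817.

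**Step 3: other readings of the same sentence.**
- *One-sided 5% t-test:* 20 evaluable (power 0.808); 20 / 0.85 = 23.5, so 24 per group (48 in total). Power at 22 per group is 0.84, so on this reading there is no shortfall, but the stated number is still not reproduced.
- *Two-sided Mann–Whitney (relative efficiency 3/π = 0.955):* 27 evaluable, 27 / 0.85 = 31.8, so 32 per group. Power at 22 per group is about 0.73.
- *One-sided Mann–Whitney, same efficiency:* 21 evaluable, 21 / 0.85 = 24.7, so 25 per group (50 in total).
- *Between-groups repeated-measures F test:* effect f = 0.81 / 2 = 0.405, noncentrality f² x N x m / (1 + (m − 1)ρ) for m measurements with correlation ρ. With m = 2 and ρ of about 0.70 to 0.75, or m = 3 and ρ = 0.80, 44 evaluable in total are needed. Then 44 / 0.85 = 51.8, so 52, or 26 per group. This matches the stated figure, but the correlations are assumptions and the article gives none.
- *Baseline-adjusted comparison at week 24:* the effective effect is 0.81 / √(1 − r²). At 22 per group, r = 0.30 gives power 0.786, r = 0.35 just about 0.80, r = 0.40 gives 0.817 and r = 0.50 gives 0.858. A baseline-to-week-24 correlation of about 0.36 or more therefore restores 0.80.

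**The case against.** The strongest reply is that the two-sided t-test is supplied by the reader. The article names no test family, the hypothesis in the Introduction is directional, and a one-sided test with 22 per group has power 0.84. Section 2.36 plans repeated-measures models, and a repeated-measures calculation with a fairly high correlation returns exactly 26 per group with the 15% included. On this view the defect is only an unreported assumption, of a kind that a condensed article may leave to the full protocol.

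Part of this stands. The shortfall is conditional, and a modest baseline correlation would remove it. But no one-sided test is declared, two-sided is the usual default, and the one-sided t-test gives 24, not 26. The repeated-measures route needs a correlation that appears nowhere. The article does not leave the calculation to another document: it states inputs and a result, and under the conventional reading the two disagree.

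It is also true that 52 is worded as a floor, so enrolling more could close the gap. It is nevertheless the number said to be required, and a trial that meets it exactly does not have the stated power under that reading.

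Two stronger readings are tempting and are not supported:
- A reader might infer that the dropout allowance was described but never applied, because 26 is close to the no-dropout requirement. The figures suggest this but do not prove it, since the repeated-measures calculation reaches 26 with dropout included.
- A reader might set the Introduction's statement that "exercise training has a moderate effect on reducing glycated hemoglobin (HbA1c) and insulin dose per day" against 0.81, and infer that the trial is badly underpowered for a smaller effect. That one adjective covers HbA1c and insulin dose jointly, and the article gives no smaller effect figure from which to compute power.

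**Conclusion.** The point holds in a limited form. For a two-sided, unadjusted two-sample t-test with the stated effect, level and dropout, 26 randomised per group gives about 0.75 power rather than 0.80; 29 to 30 per group would be needed. The size is about 5 percentage points of power or, equivalently, a detectable effect of about 0.87 instead of 0.81.

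This rests on two assumptions that the article leaves open: two-sided testing and no gain from baseline or repeated measurements. If either is dropped the shortfall may disappear, but the text would then have to say so. Type I error, the primary outcome and the planned analysis are unaffected. This should be fixed; it is not a flaw that invalidates the design.

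**What to change.** Correct section 2.32 without changing enrolment, in one of two ways:

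(a) Keep the simple calculation and report what it gives: 26 randomised per group, with 15% dropout (22 evaluable), has about 0.75 two-sided power for an effect of 0.81, or 0.80 for an effect of about 0.87.

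(b) Restate the calculation for the baseline-adjusted or repeated-measures model planned in section 2.36, giving the test, its sidedness and the assumed correlation with its justification. With baseline adjustment, a baseline-to-week-24 correlation of about 0.36 or more gives 0.80 with 22 per group.

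The cost is wording only. Option (a) makes the stated power slightly less favourable. Option (b) adds one correlation assumption that must be defended. The 52 in the abstract can stay as the enrolment minimum under either option.

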### Randomization, allocation concealment, and blinding

2.33

Participants meeting eligibility criteria will be randomly assigned to one of two groups in a 1:1 ratio using block randomization with a computer-generated schedule (Research Randomizer V.4). This will ensure equal group sizes. Randomization will continue until a predetermined number of participants are assigned. The allocation code will be kept confidential at Navarrabiomed until final analysis. To ensure blinding, each study group will be assigned an alpha-numeric code. Researchers will receive the code for their assigned group. Data analysts will not have access to the code until completing the coded intervention analysis. Due to the nature of the study, patients in the Diactive-1 App group will not be blinded.

### Procedure for unblinding if needed.

2.34

This study is an unblinded, practice-level intervention.

### Data collection methods and management

2.35

Researchers will be responsible for finalizing the study protocol and maintaining regular communication through phone calls, emails, and meetings. Weekly meetings will also be held for investigators and pediatric staff to discuss progress and updates.

The provided information will be documented in the database using individualized study codes assigned to each participant. This data will be securely stored on a computer that requires a password for access. Only the data manager, who operates independently and without conflicting interests, will have permission to access and retrieve the data. Due to the low level of risk associated with the study, there is no requirement for a Data Monitoring Committee. However, any significant modifications to the study protocol will be promptly communicated and updated on both the Clinical Trial Registry and the publication journal. Within a maximum timeframe of three years from the collection of the end-line assessment at the 24-week mark, a fully anonymized dataset will be submitted to an appropriate data archive for sharing purposes.

### Statistical methods

2.36

The quantitative variables will have their mean (M) and standard deviation (SD) provided, whereas the qualitative variables will include frequencies (n) and percentages (%). To assess data normality visual inspection of Q-Q plots and Shapiro-Wilk test will be used. For the homogeneity of variances, Levene’s test will be used. Subsequently, for two-group comparisons, either Student’s t-test or Mann–Whitney U test will be used based on adherence to the normality assumption.

Associations among qualitative variables will be examined using Pearson’s chi-square (χ²) test. For quantitative variables, the association will be tested using Spearman’s rank correlation coefficient (ρ) or Pearson’s correlation coefficient (r), depending on the assumption of normality. Initial analyses will establish frequency, range, variability, and distribution patterns of each variable, guiding the choice of the most appropriate statistical test for comparisons.

Given the experimental design of this RCT involving two data collections—baseline (t0 = 0 weeks) and post-intervention (t1, t2 = 12 and 24 weeks)—in both intervention and control groups, a comparative analysis will be conducted to identify intergroup differences. Multilevel mixed-effects regression models with repeated measures will be used to evaluate the intervention effect for each dependent variable. Multivariate analyses will account for autocorrelation between repeated measures.

For data analysis, both intention-to-treat (ITT) and per-protocol (PP) approaches will be employed. ITT measures the impact of intervention assignment, while PP analysis gauges the effect of intervention receipt. Statistical analyses will be performed using Stata software (version 17.0) (StataCorp, College Station, TX, USA), the statistical software R (Version 4.1.1) (R Core Team, Vienna, Austria), and RStudio (Version 2021.09.2) (Posit, Boston, MA, USA). Statistical significance will be determined by a p-value ≤ 0.05.

In situations where exercise sessions are missing, the analysis of outcomes will incorporate a dose-response approach. This approach will consider potential variations in outcome measurements based on the degree of exposure to the intervention. Additionally, depending on the nature of the missing data for both primary and secondary outcome measures, a range of techniques like multiple imputation, listwise deletion, or specific analytical methods will be employed. These measures aim to mitigate the impact of missing data, thereby minimizing any potential reduction in the generalizability of the collected data (61).

Subgroup analyses will be carried out to ascertain whether exercise is more or less effective in reducing secondary outcomes compared to the waiting-list control group. These subgroup analyses will adhere to the same methodology as the primary analysis, including both the primary analysis variables and their interaction with the experimental condition.

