### Primary outcome

2.9

The primary outcome measure is the daily insulin dosage requirement. Participants will maintain a diary for nine days, recording their carbohydrate intake and insulin doses. This diary will record information about insulin injections. Children and adolescents who use an insulin pump will be assessed by obtaining objective information through downloading their data. The collected information will be used to calculate the insulin units per day per kilogram of body weight. A comparison will be made by providing participants with the same diary again, both at 12 weeks into the intervention and 9 days before the intervention concludes at week 24.

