### Participant timeline

2.31

Eligible and consenting participants will complete a baseline assessment. The intervention group will then be allocated to a 24-weeks exercise training program using the Diactive-1 App. The control group will continue standard care. Outcomes will be assessed at baseline (T0), 12-week (T1) and after the 24-week intervention period (T2) (**Table 2**).

**Table 2 T2:** Schedule depicting the enrollment and interventions for the Diactive-1 Study in accordance with the SPIRIT 2013 guidelines ^26^.

TIMEPOINT	STUDY PERIOD				
	Enrolment	Allocation		Post-allocation	
	*-t_1_ *	0	*Baseline* *(T0)*	*T_1_ * * _(12 weeks)_ *	*T_2_ * * _(24 weeks)_ *
ENROLMENT:					
Eligibility screen	X				
Informed consent	X				
Allocation		X			
INTERVENTIONS:					
*Diactive-1*		X			
*Waiting-list control group*		X			
ASSESSMENTS:					
*Daily insulin dosage requirement*			X	X	X
*Glycemic control (time in range, glucose coefficient of variation, number of hypoglycemic and hyperglycemic events)*			X		X
*Cardiovascular biomarkers (of fasting glucose, glycated hemoglobin, triglycerides, high-density lipoprotein cholesterol, low-density lipoprotein cholesterol, apolipoproteins, alanine aminotransferase, and aspartate aminotransferase)*			X		X
*Anthropometric parameters (body weight, standing and sitting height)*			X		X
*Sexual maturation and peak height velocity*			X		X
*Body composition parameters (total body fat, lean mass, subcutaneous and visceral adiposity, bone mineral content and density)*			X	X	X
*Heart rate variability*			X		X
*Vascular function*			X		X
*Physical fitness components (cardiorespiratory and muscular fitness)**			X	X	X
*Physical activity, sedentary time, and sleep duration by accelerometers and questionnaires **			X	X	X
*Sleep quality*			X		X
*Inadvertent hypoglycemia*			X		X
*Psychological assessments (Health-Related Quality of Life and subjective well-being)*			X		X
*Diet (adherence to the Mediterranean diet and food consumption)*			X		X
*Eating disorders*			X		X
*App usability*					X

* It will only evaluate handgrip strength and accelerometer-based physical activity at 12-week mark. T, represents a time-point.

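### The repeated-measures model lists baseline among the data collections but states neither a baseline covariate nor equal arm means at baseline; on its natural reading the week-24 effect is less precise than a baseline-adjusted one

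*Protocol article*

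**What the plan says.** The primary outcome is insulin dose per kilogram (section 2.9): "The collected information will be used to calculate the insulin units per day per kilogram of body weight". Everyone supplies a baseline value before the intervention starts (section 2.31): "Eligible and consenting participants will complete a baseline assessment". The same section fixes the follow-up visits at 12 and 24 weeks, and Table 2 marks insulin dose at T0, T1 and T2.

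Section 2.36 describes the design as "two data collections—baseline (t0 = 0 weeks) and post-intervention (t1, t2 = 12 and 24 weeks)—in both intervention and control groups". The next statement on method is "Multilevel mixed-effects regression models with repeated measures will be used to evaluate the intervention effect for each dependent variable", followed by a sentence that autocorrelation between repeated measures will be accounted for. No fixed terms, contrast, baseline covariate or baseline constraint are given.

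The opening paragraph of section 2.36, beside the descriptive statistics and normality checks, also says "for two-group comparisons, either Student’s t-test or Mann–Whitney U test will be used based on adherence to the normality assumption". That sentence names no outcome, no visit, and neither raw nor change values.

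**The concern.** Baseline dose is available for every randomised child and is likely to predict the week-24 dose. Randomisation makes the true arm difference at baseline zero. A model that treats baseline as a response and leaves the arm means free at T0 still estimates that difference and subtracts it. This adds noise to the effect and carries any chance imbalance into it with the sign reversed.

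The text supports reading baseline as a response. Section 2.36 applies the repeated-measures model to every dependent variable, yet Table 2 schedules most secondary outcomes (for example CGM metrics, blood biomarkers, vascular function and quality of life) at T0 and T2 only. With one follow-up value, a repeated-measures model exists for those outcomes only if baseline is one of the responses.

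Precision matters here because the trial is small, ages run from 8 to 18 years, and section 2.33 describes block randomisation without naming stratification. A sizeable chance difference in baseline U/kg/day would be no surprise.

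**Working it through.** **Inputs from the article (section 2.32).** Standardised effect 0.81, power 0.80, significance level 0.05, dropout 15%, 26 per arm. Evaluable per arm: 26 × 0.85 = 22.1, taken as 22.

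**Assumptions not in the article.** Two-sided testing; rho, the correlation between baseline and week-24 dose, shown over a range; equal SDs at the two visits; 0.81 expressed in SDs of week-24 values; complete data.

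**The plan's own figure.** A two-sided two-sample t-test with d = 0.81 needs 25 evaluable per arm for 80% power, and 25/0.85 = 29.4, so 30 to recruit. The stated 26 is not reproduced that way. Sidedness is not stated: one-sided gives 20 evaluable and 24 recruited, and two-sided without a dropout allowance gives 25. That is a separate matter. For this point, it means only that an unadjusted two-sided comparison of 22 per arm has power 0.75.

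**Variances**, relative to a plain week-24 difference (= 1):
- difference in change (free baseline means, arm-by-visit effect): 2(1 − rho)
- baseline-adjusted: 1 − rho²
- ratio, adjusted to change: (1 − rho²)/(2(1 − rho)) = (1 + rho)/2

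Generalised least squares for three visits under compound symmetry confirmed these. At rho 0.5, 0.6, 0.7 and 0.8, the free-means arm-by-visit contrast had relative variance 1.00, 0.80, 0.60 and 0.40. With baseline kept as a response but arm means constrained equal at T0, it was 0.75, 0.64, 0.51 and 0.36, the same as covariate adjustment.

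**Power at 22 per arm** (noncentral t; 42 df for change, 41 for adjusted). Effective effect: 0.81/√(2(1 − rho)) for change, 0.81/√(1 − rho²) for adjusted.

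| rho | effect, change | effect, adjusted | power, change | power, adjusted | gain (points) | variance cut |
|---|---|---|---|---|---|---|
| 0.5 | 0.81 | 0.94 | 0.75 | 0.86 | 11 | 25% |
| 0.6 | 0.91 | 1.01 | 0.84 | 0.91 | 7 | 20% |
| 0.7 | 1.05 | 1.13 | 0.92 | 0.96 | 3 | 15% |
| 0.8 | 1.28 | 1.35 | 0.99 | 0.99 | 1 | 10% |

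Gains come from unrounded powers. Below 0.5 the gap widens: 0.60 against 0.79 at rho 0.3, and 0.67 against 0.82 at rho 0.4.

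**If 0.81 is in SDs of change instead.** The change contrast then has power 0.75 at every rho, and the adjusted effect is 0.81 × √(2/(1 + rho)). Adjusted power is 0.86, 0.83, 0.81 and 0.79 at rho 0.5, 0.6, 0.7 and 0.8: gains of 11, 9, 6 and 4 points.

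**Chance imbalance.** Given an observed baseline difference b (in SDs), the change contrast is centred on the true effect minus (1 − rho)b; the adjusted estimate is not shifted. The standard error of b at 22 per arm is √(2/22) = 0.30 SD. An imbalance of that size moves the change contrast by 0.15 SD at rho 0.5 and 0.06 SD at rho 0.8.

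**The case against.** The strongest reply is that the criticised model is not written down. Section 2.36 names a class of model, and listing t0 with t1 and t2 may describe the data rather than the response vector. A model of weeks 12 and 24 with a baseline covariate, or one with constrained baseline means, also fits the sentence. Exact terms are often left to an analysis plan, which is not shown here. Much of this stands: the article does not exclude adjustment, and under a constrained model the loss is zero. But the list of collections, together with one model for outcomes measured only at T0 and T2, makes baseline-as-response the natural reading, and nothing in the text points to the constraint.

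It is also fair that the change contrast is unbiased over randomisation with valid type I error, that rho is unknown, that the gain is slight when rho is high, and that a mixed model can use week-12 data from children who later leave, so 22 complete cases is a simplification.

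A reader might go further and infer that the t-test or Mann–Whitney sentence is a second route to the 24-week comparison that ignores baseline, so that one stated analysis must lose materially whatever rho is. The article does not support that. The sentence is generic and sits with the descriptive material, while the method named for the intervention effect is the mixed model. Section 2.9 also speaks of a comparison made by repeating the diary, which suggests that follow-up is set against baseline.

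**Conclusion.** The point holds as one of efficiency and clarity: the arm-by-visit contrast is not invalid. As described, the most natural form of the primary model gives a week-24 effect whose variance is 2/(1 + rho) times that of the baseline-adjusted effect, which is 1.33 times at rho 0.5 and 1.11 times at rho 0.8. The corresponding power gain is about 11 points falling to 1, on the assumed rho, 22 per arm, two-sided testing and 0.81 in SDs of week-24 values. On the change-SD reading of 0.81 it is 11 falling to 4. The size therefore depends on a correlation that the article does not give.

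It would be too strong to say that the plan discards baseline information outright: the fixed terms are unstated, and a constrained-baseline model would lose nothing. The change is still worth making, because it is nearly free and it settles which contrast is the treatment effect.

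**What to change.** In section 2.36, state that the primary effect is the baseline-adjusted arm difference in insulin U/kg/day at week 24. Obtain it from either:
- a mixed model with weeks 12 and 24 as responses and arm, visit, arm-by-visit, baseline dose and baseline-by-visit as fixed terms, with within-child correlation; or
- a mixed model with all three visits as responses and the arm means constrained equal at T0.

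For secondary outcomes measured only at T0 and T2, use ANCOVA on the T0 value or the constrained model. State that the t-test or Mann–Whitney comparison is descriptive and does not test the intervention effect.

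The cost is one or two sentences and about one degree of freedom, with no new data, visits or participants. The covariate form needs a simple imputation for a child without a baseline diary; the constrained form avoids this.
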